**Subjects:**

We will assess 504 patients (252 in each group) aged > 50 years assigned to 25 primary healthcare centers (PHC) from Catalonia (urban, semi-urban, and rural). Participants suffer from major depression (Beck depression inventory: BDI-II 13–28) and at least one of the following: type 2 diabetes mellitus, chronic obstructive pulmonary disease, asthma, and/or ischemic cardiopathy. Patients with moderate/severe suicide risk or severe mental disorders are excluded. Participants will be distributed randomly into the intervention group (IG) and control (CG).

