### Sample

The participants are patients aged > 50 years assigned to PHC from different locations: Barcelona city (1,200,066), the central area of Catalonia (192,000), and the southern area (132,000). Such a territorial representation provides patients from urban, semi-urban, and rural areas.

Inclusion criteria are: 1) the presence of at least one of the following physical diseases: diabetes mellitus type 2, COPD, asthma, and ischemic cardiopathy; 2) a score > 12 on the Beck Depression Inventory score (BDI-II) [21, 22] Spanish version adapted by Sanz et al. [23–25], and confirmation of major depression according to DSM-IV criteria with the Mini International Neuropsychiatric Interview (MINI); 3) adherence to a one-year follow-up with the same PHC team; 4) signed informed consent.

Exclusion criteria are: 1) diagnosis of dementia or moderate/elevated cognitive decline (5 or more errors on the Pfeiffer scale); 2) major depressive disorder with psychotic symptoms or other serious psychiatric comorbidities; 3) elevated/moderate risk of suicide (a score of ≥6 on the MINI scale); 4) drug of abuse dependence disorders (including alcohol); 5) physical illness at an advanced stage; 6) inability to attend the PHC; 7) under psychological therapy from the Community Mental Health Team; 8) inability to understand Spanish/Catalan.

Patients receiving anti-depressive/anxiolytic treatment are not excluded. Their data are collected and considered as covariables.

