### Sample size

A power analysis will be conducted to determine the appropriate sample size. A previous study of psychoeducation programs [18] reported a remission rate at 9 months follow-up of 40% in the IG and 26% in the CG. Assuming a 5 and 20% alpha and beta risk, respectively, 189 patients are required for each group. Due to a number of reasons, an approximately 25% dropout rate is expected, consequently, 252 participants per group need to be recruited (total *n* = 504). In addition, 25 PHC are required each with a mean of 20 patients (IG *n* = 10, CG *n* = 10).

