Sex, age, civil status, educational level (without studies / incomplete primary ones / completed primary ones / secondary ones / higher education), employment status (employed / housewife / unemployed / disabled / retired). Assigned PHC: rural (doctor’s surgery) / semi-urban (PHC with a population < 15,000 inhabitants) / urban (PHC with a population ≥ 15,000 inhabitants).

Primary outcomes*Clinical remission and/or response of depression* at short and long-term (one year follow-up) of the intervention following Riedel et al. [32]: clinical remission considered as a reduction in the rating < 13 of the BDI-II; response to the intervention as a decrease of at least 50% in the initial evaluation of depressive symptoms according to the BDI-II.

Secondary outcomes

*Improvement in the control of the chronic pathology* at 12 months follow-up:
Diabetes mellitus: controlled with glycosylated hemoglobin, HBA1C (%) [33, 34].COPD: lung function measured by post bronchodilator expiratory volume (FEV1). Dyspnea evaluated by the modified score of the Medical Research Council (mMRC), at 5 points [35, 36]Asthma: lung function measured by post bronchodilator expiratory volume (FEV1). Determination of peak expiratory flow (PEF) [37].Ischemic cardiopathy: measurement of levels of low-density lipoprotein cholesterol and blood pressure [38].
2.*Adherence to medication* is assessed by the *Morinsky-Green* test [39] and the comparison between containers collected in the pharmacy and those prescribed. It will be performed for all the prescribed medication for both groups.3.*Quality of life* as measured with the *EuroQol (EQ-5D-5 L)* questionnaire. (Original: EuroQol Group 1996. Spanish adaptation: Badia et al. 1999) [40, 41].4.*Utilization of healthcare services* during the study period. This includes: number of hospital admissions (emergency room and ward) due to complications arising from diabetes, COPD, and ischemic cardiopathy (yes/no), and psychiatric pathology (yes/no); mental health referrals (yes/no) and number; and consultations with the family doctor/nurse (yes/no) and number.5.*Variables resulting from the intervention with respect to its feasibility.* A questionnaire with 10 items and a Likert scale of 4 categories regarding satisfaction is administered to the patients on completing the intervention. Adherence is assessed through the number of sessions each IG patient attends. An adherence variable is calculated for the intervention: ≥75% attendance or less.

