### Statistical analysis

The analysis is performed on an intention-to-treat basis. All the patients who have signed the informed consent and attended the initial interview are included. Missing data from the BDI-II evaluation during follow-up will be substituted by the last registered value (Last Observation Carried Forward strategy). At the beginning of the study descriptive statistics will be performed to evaluate the homogeneity between the two groups (IG and CG) with respect to demographic, clinical, and service utilization variables. In order to measure the main objective (rate of remission and response) logistic regression is employed in which the dependent variable is dichotomous (rate of remission and response). The patient’s group is the independent variable. Raw and adjusted odds ratio (OR) are calculated according to age, sex, pharmacologic treatment, and comorbidity. Repeated measure ANOVA analysis will be performed to determine the evolution of the dependent variables during follow-up. For the secondary resulting variables, control of the physical pathologies will be measured by logistic regression in which the dependent variable is dichotomous (control yes/no). The models will be adjusted in the same way as the principal one. Variable differences in the BDI-II rating and other scores with respect to baseline will be calculated. Student’s t test will be employed for the comparison between the groups’ variables and standardized effect size (SES; Kazis et al.1989) [44].

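### The remission cut-off adjoins the entry cut-off, so success depends strongly on baseline BDI-II, yet the planned models leave baseline out

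*Protocol article*

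**What the plan says.** **Entry.** The inclusion criteria (Sample) require "a score > 12 on the Beck Depression Inventory score (BDI-II", with major depression confirmed by the MINI. Neither the inclusion nor the exclusion list sets an upper limit. The Abstract (Subjects) does give one: "Participants suffer from major depression (Beck depression inventory: BDI-II 13–28".

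**Primary outcome.** Measures names "Clinical remission and/or response of depression". Its parts are "clinical remission considered as a reduction in the rating < 13 of the BDI-II" and "response to the intervention as a decrease of at least 50% in the initial evaluation of depressive symptoms according to the BDI-II". The remission definition cites a published source.

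**Analysis.** The Statistical analysis section uses logistic regression in which "the dependent variable is dichotomous (rate of remission and response". The adjusted odds ratio takes account of age, sex, drug treatment and comorbidity; baseline BDI-II is not listed. Changes in BDI-II from baseline are compared by Student's t test with a standardized effect size, and a repeated-measures ANOVA follows the course over time.

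**Planning rates.** Sample size rests on remission alone: "a remission rate at 9 months follow-up of 40% in the IG and 26% in the CG".

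**The concern.** The lowest qualifying score (13) and the highest remission score (12) are neighbours. Patients at the bottom of the entry range can cross the line with a very small change, while those higher up must improve a great deal. Three things follow.

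- A remission does not mean the same improvement in every patient.
- The 50% response criterion, which looks like a second route to success, is contained in remission over much of the entry range.
- Baseline BDI-II becomes a strong predictor of the primary outcome, so leaving it out of the adjusted model gives up precision.

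In addition, the two descriptions of the composite and the two entry ranges lead to different answers on how much each component contributes.

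**Working it through.** **1. The plan's own figure.** Inputs: 40% and 26%, alpha 5% (taken as two-sided), power 80%. The mean rate is 0.33 and the difference 0.14.

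n = [1.960 × √(2 × 0.33 × 0.67) + 0.842 × √(0.40 × 0.60 + 0.26 × 0.74)]² / 0.14² = 175.9.

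With continuity correction: (175.9 / 4) × [1 + √(1 + 4 / (175.9 × 0.14))]² = 189.9. This agrees with the stated 189 to within rounding. Dropout: 189 / 0.75 = 252, as stated. The sample size arithmetic is sound and this point does not change it.

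**2. Smallest fall that counts.** For a whole-number baseline b, remission needs a fall of b − 12. Response needs a fall of b/2, rounded up.

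| Baseline | Fall for remission | As % of baseline | Fall for 50% response |
|---|---|---|---|
| 13 | 1 | 7.7 | 7 |
| 14 | 2 | 14.3 | 7 |
| 16 | 4 | 25.0 | 8 |
| 20 | 8 | 40.0 | 10 |
| 24 | 12 | 50.0 | 12 |
| 28 | 16 | 57.1 | 14 |

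Remission is the easier criterion for every baseline below 24. The two need the same fall at 24 and 25, and response is easier from 26 upwards.

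**3. Response without remission.** This needs a follow-up score of at least 13 and at most b/2, so b must be at least 26. Up to 28 the only cases are 26 (score 13), 27 (score 13) and 28 (scores 13 and 14). Without a cap the window widens: at baseline 40 it is 13 to 20.

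**4. Share of successes due to response alone.** The article gives no BDI-II distribution, so this is illustrative. Assumptions: normal baseline, mean 20 to 30 and SD 6 to 10 before truncation at entry; follow-up SD about 10; correlation 0.5; mean fall 3 to 10 points.

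- Baseline capped at 28: 1% to 5% of successes.
- No cap: about 3% if the mean baseline after truncation is near 21, about 10% near 24, 20% to 22% near 27, and 35% to 39% near 31.

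**5. How far baseline drives remission.** Assume no mean change and a normal change with SD 3, 5 or 7. The chance of scoring 12 or less is Φ((12.5 − b) / SD).

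- b = 13: 43%, 46%, 47%.
- b = 16: 12%, 24%, 31%.
- b = 20: 1%, 7%, 14%.

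**6. Change score against ANCOVA.** With baseline SD σb, follow-up SD σf and correlation ρ, the change score has variance (σb − ρσf)² + σf²(1 − ρ²). ANCOVA leaves σf²(1 − ρ²), which is never larger. With equal SDs the ratio is (1 + ρ)/2, so at an assumed ρ of 0.5 it is 0.75. If truncation at entry makes σb close to ρσf, the gain is small.

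**The case against.** The remission cut-off follows a cited source. Chance crossings occur in both randomised arms alike, so the comparison is not biased. The plan already defines response and already compares BDI-II changes, so small falls would be visible. Covariate choice is often settled in an analysis plan, which is not shown. Most of this stands, and it is why the cut-off should stay. But the article does not leave the adjustment set open: it lists the covariates, and baseline BDI-II is not among them.

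A reader might infer several stronger points that the documents do not support.

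- **The composite is simply remission.** That needs the ceiling of 28, which is only in the Abstract. Under the inclusion criteria as written, response may supply a material share of events.
- **A 1-point fall is definitely a success.** That holds under the and/or definition in Measures. If the Statistical analysis wording means that both are required, a 1-point fall fails and response is the binding part for baselines up to 25.
- **Most remissions would be trivial.** With baseline uniform on 13 to 28, change SD 4 to 8 and mean change 0 to −4, 31% to 86% of remissions are falls of less than 50%. That grid reaches only about 33% remission, short of the planned 40%. At mean change −6, remission is 38% to 41%, falls under 50% make up 26% to 50% of remissions, and falls of 3 points or fewer about 4% to 7%.
- **Noise explains much of the planned control rate.** An observed 26% already includes chance remissions, and the article does not show which remission definition lies behind it.

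**Conclusion.** The concern holds in a limited form. It is certain from the definitions that the cut-offs adjoin, that remission is the easier criterion below a baseline of 24, and that response implies remission for baselines 13 to 25. It is also certain that the listed adjustment set omits baseline BDI-II and that the score comparison is a t test on change. The 1-point success depends on the and/or reading. How little response adds depends on the entry range: four score pairs under 13 to 28, and possibly more than a third of successes without a cap if mean baseline is near 31.

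The consequence is lost precision and a composite that is hard to interpret. The size of the precision loss cannot be fixed from the article, because it gives neither SDs nor a correlation. This is worth correcting, but it does not threaten the validity of the randomised comparison.

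**What to change.** 1. Add baseline BDI-II to the covariates of the adjusted logistic model.
2. Analyse the 12-month BDI-II score by ANCOVA on baseline, in place of the t test on change.
3. Report remission and 50% response separately, beside the composite.
4. State whether the composite requires either component or both, so that Measures and Statistical analysis agree.
5. Reconcile the entry range in the Abstract with the inclusion criteria.

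Keep the cited remission cut-off. A further outcome that combines remission with a 50% fall is not needed: for baselines 13 to 25 it is identical to the response already defined, and up to 28 it differs in only four score pairs.

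The cost is a few lines of wording and slightly more analysis. BDI-II is already collected at baseline, 3 months and 12 months, and the sample size does not change.

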**Secondary measurements:**

Improvement in control of chronic diseases (blood test and physical parameters), drug compliance (Morinsky-Green test and number of containers returned), quality of life (EQ-5D), medical service utilization (appointments and hospital admissions due to complications), and feasibility of the intervention (satisfaction and compliance). Evaluations will be blinded, and conducted at baseline, post-intervention, and 12 months follow-up.

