### Measures

The selected variables and instruments, as well as the evaluation program timeline, are detailed in Table 3. Data will be imported using an online survey tool and include:

**Table 3 Tab3:** Outcome measures

Outcome measures	Timeline		
	Pre-intervention	Post-intervention	
		3 mo	12 mo
1. Socio-demographic variables			
Sex, age, marital status, educational level, employment status, reference PHC	X		
2. Diagnostic variables			
Diagnosis depression: MINI	X		
Diagnosis chronic physical illness: ICD-10	X		
Suicide risk: MINI	X		
Cognitive impairment: Pfeiffer questionnaire	X		
3. Clinical variables			
Depressive symptoms: BDI- II questionnaire	X	X	X
Anxiety symptoms: HARS questionnaire	X	X	X
Quality of life: EQ-5D-5 L questionnaire	X	X	X
Pharmacotherapy	X	X	X
Therapeutic compliance: Morinsky-Green test	X	X	X
Feasibility of the intervention	X	X	
4. Blood test and Physical parameters			
Type 2 diabetes mellitus: Analytical HBA1C	X		X
COPD: FEV1 and Medical Research Coincil (mMRC)	X		X
Asthma: Spirometry and Peak flow	X		X
Ischemic heart disease: Analytical cholesterol LDL and Blood pressure	X		X
5. Costs variables			
Pharmacological Treatment	X	X	X
Utilization of services: PHC and hospital	X	X	X
Other comorbidities	X		X
Costs derived from the intervention	X	X	X

*Abbreviations*: *mo* months, *BDI-II* Beck Depression Inventory secondary edition, *COPD* Chronic obstructive pulmonary disease, *EQ* EuroQuol, *FEV1* Forced expiratory volume, *HARS* Hamilton Anxiety Rating Scale, *HBA1C* Hemoglobin A1C test, *ICS-10* International classification of diseases-10th revision, *MINI* Mini international neuropsychiatric interview, *PHC* Primary Healthcare Centers

Diagnostic variables*Diagnosis of depression* according to the MINI interview [27, 28].*Physical diseases* (code CIE-10). Diagnosis of diabetes mellitus (E11-E14 and sub-groups), COPD (J43-J44 and sub-groups), asthma (J45), and/or ischemic cardiopathy (I20-I25 and sub-groups) as registered in the patients’ medical records and confirmed by their family doctor [29].*Risk of suicide* evaluated by the MINI interview [27, 28].*Pfeiffer Scale* to detect cognitive impairment [30, 31]. This is a hetero-administered questionnaire made up of 10 items and scored from 0 to 10 (errors). From 5 onwards an individual is considered to present moderate/severe cognitive decline.

Socio-demographic variables:

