Confounding variables and effect modifiers*Pharmacological treatment.* The defined daily dose for each active ingredient is established during the follow-up period taking into account the number of days, the dosage, and the route of administration. The registered active ingredients belong to the following groups: antidepressants, anxiolytics, antidiabetics (oral, insulin), bronchodilators (selective agonists of Beta2 - adrenergic, anticholinergic), anti-inflammatories: corticosteroids, antihypertensives, and dyslipidemics.*Other associated comorbidities:* cardiac insufficiency, atrial fibrillation, cardiovascular disease, peripheral vascular disease, other chronic diseases.Participation in *other mental health therapies* given by psychologists and psychiatrists.*Anxiety* evaluated with the HARS-Hamilton Anxiety Rating Scale [42].*History of previous depressive episodes* (yes/no).

Cost variables

Expenses included in the cost-effectiveness analysis:*Use of primary care services*: consultation fees according to professional status and level of care.*Use of hospital services*: hospitalization and emergency room consultations.*Cost of psychotropic medication consumed during the study*: anxiolytics and antidepressants according to the current catalogue from the Pharmacist Association.*Derived costs*: training and supervision of the nurses responsible for leading the sessions, their working hours spent with the groups, and expenses related to material used in the sessions and given out to the participants. In order to calculate the cost of the resources 2016 Oblikue rates are employed [43].

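### The container-based adherence measure is defined in two incompatible ways, and its stated scope has no exception for medicines that may be prescribed as needed

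*Protocol article*

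**What the plan says.** Three places in the protocol article describe how adherence to medication is measured.

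- **Abstract, Secondary measurements:** "drug compliance (Morinsky-Green test and number of containers returned".
- **Measures, Secondary outcomes, item 2:** the Morinsky-Green test together with "the comparison between containers collected in the pharmacy and those prescribed. It will be performed for all the prescribed medication for both groups". The second sentence of this quote sets the scope.
- **Measures, Table 3:** the only compliance row is "Therapeutic compliance: Morinsky-Green test", marked at baseline, 3 months and 12 months. No row names containers.

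On which drugs may be involved, the Sample section admits patients with asthma or COPD and does not exclude those on antidepressant or anxiolytic treatment. The list of confounders and effect modifiers in Measures registers, among others, "antidepressants, anxiolytics, antidiabetics (oral, insulin), bronchodilators (selective agonists of Beta2 - adrenergic, anticholinergic". No section separates medicines prescribed for regular use from medicines prescribed as needed.

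**The concern.** There are two issues, and they differ in certainty.

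The first is in the text itself. A count of containers returned and a comparison of containers collected with containers prescribed are not the same variable. The first is taken after dispensing and has no stated denominator. Even its direction is unclear, since a high count could mean empties from good use or unused stock from poor use. The second measures how far prescriptions are filled. A reader of the article cannot tell from the abstract which of them will be reported.

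The second is conditional. The Measures text applies the comparison to every prescribed medicine. For a medicine prescribed as needed, collecting less than the prescribed amount is not in itself poor adherence, because it can mean that the patient needed less. The programme aims to improve depression and control of the physical disease, and session 6 covers therapeutic compliance. If it succeeds, as-needed use may fall in the intervention group while adherence to regular medicines holds or rises. A comparison that mixes the two kinds of medicine could then move against the intervention on an outcome that the programme directly targets.

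**Working it through.** **Step 1: the definitions side by side.** The plan states no figure for this outcome, so there is none to reproduce.

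| Place | Container quantity | Denominator | Drugs covered |
|---|---|---|---|
| Abstract, Secondary measurements | returned | none stated | not stated |
| Measures, Secondary outcomes, item 2 | collected at the pharmacy | prescribed | all, both groups |
| Table 3 | none (Morinsky-Green only) | – | – |

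The first two rows cannot both describe the same variable. No section describes patients handing containers back, and Table 3 does not settle the matter.

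**Step 2: what an unrestricted scope can do to the score.** The article gives neither the share of prescribed containers that are as-needed nor how many of those are collected, so both are assumed and varied. Let R be the regular containers prescribed, all collected; P the as-needed containers prescribed; and f the fraction of P collected. With containers pooled over drugs and P held fixed:

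score = (R + f × P) / (R + P)

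| R + P | As-needed share P/(R + P) | f = 1 | f = 0.75 | f = 0.50 | f = 0.25 |
|---|---|---|---|---|---|
| 48 + 12 | 20% | 100% | 95.0% | 90.0% | 85.0% |
| 36 + 12 | 25% | 100% | 93.8% | 87.5% | 81.2% |
| 24 + 12 | 33% | 100% | 91.7% | 83.3% | 75.0% |

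For the lowest cell: (24 + 0.25 × 12) / 36 = 27/36 = 75.0%.

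Restricted to regular medicines, the score is R/R = 100% in every cell. The whole shortfall in the table therefore comes from as-needed medicines, for a patient who has missed nothing prescribed for regular use.

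**Step 3: when the effect disappears.** If the prescribed amount falls with need, P in the denominator becomes f × P and the score is (R + f × P)/(R + f × P) = 100%. If the comparison is made drug by drug, regular medicines still show 100% and any shortfall stays with the as-needed drug, although that drug would still be scored as under-collected.

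**The case against.** The strongest reply is that the mismatch is a slip of the pen. The word returned occurs once, in a compressed list in the abstract. The Measures section is more specific and would naturally govern. That is plausible, and it makes the correction easy. It does not remove the need for one, because the abstract still misdescribes a named secondary outcome.

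The second reply is that as-needed medicines are not in the document at all. This is correct. The drug classes are listed as confounders and effect modifiers, not in the adherence definition, and a class name does not show how a medicine is prescribed. The article also speaks only of a comparison and does not say that containers are summed over drugs. Such operational detail may stand in a fuller document that is not shown. What remains is that the scope is stated and has no exception. It is a published rule, not an omission.

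A reader might infer three stronger things, none of which the article supports:

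- **That the outcome is certainly biased against the intervention.** This needs as-needed prescribing, pooling with regular drugs, a prescribed amount that stays fixed, and a fall in need in the intervention group. None of these is documented.
- **That the distortion is large.** A steeper example is easy to build: with 6 regular and 6 as-needed containers and only 2 of the latter collected, the score is (6 + 2)/12 = 67%. Nothing in the article supports choosing those inputs, and a single patient's score is not a between-group effect.
- **That centers will collect different data.** Nothing suggests that they work from the abstract.

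**Conclusion.** The contradiction between the abstract and the Measures section is established from the text, and the two must be reconciled.

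The scope point holds as a conditional weakness. Under the Measures rule, any medicine prescribed as needed and collected below the prescribed amount would count as non-adherence, and this may work against the intervention. It rests on three assumptions that the article does not state: some of the covered medicines are prescribed as needed, they are pooled with regular ones, and the prescribed amount is not reduced as need falls. Under the assumed 20–33% as-needed share with 25–100% of those containers collected, a patient fully adherent to regular medicines would score 75–100%. That range shows what is possible; it is not an estimate for this trial.

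The consequences are confined to one component of one secondary outcome. The Morinsky-Green test, the primary outcome and the sample size are untouched. The point is worth correcting but does not threaten the main result.

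**What to change.** 1. Use one definition throughout: containers collected at the pharmacy against those prescribed, as in Measures, Secondary outcomes, item 2. Replace the reference to returned containers in the abstract, and add a matching row with its time points to Table 3.
2. Compute the adherence comparison only for medicines prescribed for regular use.
3. Report consumption of as-needed medicines separately, labelled as use and not as adherence.

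The cost is a wording change in the abstract and in Measures, a narrower list of drugs in the adherence measure, and a regular/as-needed flag when prescriptions are extracted. The article already plans to register days and dosage for each active ingredient, so the flag is a small addition. No extra patients or visits are needed, and treatment does not change.

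### The admissions outcome names three of the four qualifying diseases, so asthma admissions are not events in it

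*Protocol article*

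**What the plan says.** Inclusion criterion 1 (protocol article, Sample) requires at least one of four physical diseases: "diabetes mellitus type 2, COPD, asthma, and ischemic cardiopathy". The abstract and the objectives at the end of the Background name the same four.

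The diagnostic variables under Measures give asthma its own code, distinct from COPD: "COPD (J43-J44 and sub-groups), asthma (J45"). Asthma also has its own row in Table 3 and its own entry in the first secondary outcome, on control of the chronic disease: "Asthma: lung function measured by post bronchodilator expiratory volume (FEV1"), with peak expiratory flow.

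The fourth secondary outcome, use of healthcare services, includes the number of emergency and inpatient admissions "due to complications arising from diabetes, COPD, and ischemic cardiopathy (yes/no"), together with admissions for psychiatric illness, mental health referrals, and family doctor or nurse consultations. Asthma does not appear in that item.

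**The concern.** An outcome that counts admissions by cause should cover the diseases that define the population. Here one of the four is absent, with no stated reason. An emergency visit or ward stay for asthma would fall outside the count, while the patient stays in the denominator under the intention-to-treat rule in Statistical analysis. At stake is whether a named secondary outcome is complete. If the list is left as it is, someone will also have to decide, possibly after seeing the data, whether asthma admissions count.

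**Working it through.** The plan gives no figure for this outcome, so the check sets the disease lists side by side.

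| Place in the protocol article | Diabetes | COPD | Asthma | Ischemic heart disease |
|---|---|---|---|---|
| Sample, inclusion criterion 1 | yes | yes | yes | yes |
| Measures, diagnostic codes | yes | yes | yes | yes |
| Measures, Table 3, physical parameters | yes | yes | yes | yes |
| Measures, secondary outcome 1 (disease control) | yes | yes | yes | yes |
| Measures, secondary outcome 4 (admissions) | yes | yes | **no** | yes |

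1. *Can COPD absorb asthma?* No. COPD is J43-J44 and asthma is J45, so an admission coded to asthma does not fall under the COPD item.
2. *Is asthma added elsewhere?* No. The abstract describes the outcome as "medical service utilization (appointments and hospital admissions due to complications"), with no disease list. It neither excludes asthma nor adds it. The Measures text is the only detailed definition shown.
3. *What follows for a patient?* Someone with asthma and, say, diabetes can have a diabetes admission counted but not an asthma one. Someone who qualified by asthma alone cannot have an admission counted for the qualifying disease. A psychiatric admission could still count.
4. *Do costs inherit the gap?* No. The cost variables take "hospitalization and emergency room consultations" without limit by cause, and the economic analysis in Statistical analysis covers all direct expenses of the participants in both groups. Asthma admissions are therefore costed.
5. *Are the data there?* Table 3 collects use of primary care and hospital services at all three time points, with no restriction by disease.
6. *How many admissions are missed?* This would be the number of patients with asthma multiplied by the asthma admission rate over follow-up. The article gives neither, so it cannot be computed.

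**The case against.** The strongest reply is that this is a drafting slip of one word in one component of one secondary outcome, in an article that condenses a fuller protocol. The item is introduced as a list of what is included, the abstract carries no disease restriction, and hospital use is collected for any cause. This stands as far as it goes, and it is why the point is minor. It does not remove the point. The introductory word opens the components of service use (admissions, referrals, consultations), not the list of causes inside the admissions component. That list is stated, not left to another document.

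A reader might infer more than the text supports:

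- *That the costs are also incomplete.* They are not; hospital costs are unrestricted by cause. Applying a four-disease list to them would narrow the economic evaluation.
- *That the treatment effect is diluted.* The same definition applies to both randomized arms. Dropping one cause lowers the event count and hence precision. It would shrink a relative effect only if the effect on asthma admissions were larger than on the others, and nothing in the article says so.
- *That the Background's own rationale is contradicted.* Its example of exacerbations leading to emergency and hospital care concerns COPD, which is in the list.
- *That a count of affected patients measures the loss.* If asthma were assumed present in 10% to 25% of the 504 patients, that would be 0.10 × 504 ≈ 50 to 0.25 × 504 = 126 patients. The shares have no source in the article. The result also counts patients with asthma, some with a second listed disease, and not missed admissions.

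**Conclusion.** The inconsistency holds and is minor. As defined, the admissions component of secondary outcome 4 leaves out one of the four target diseases without explanation. It therefore undercounts target-disease admissions and gives up some precision. The size of the undercount is unknown, because neither the disease mix nor admission rates are given, and it could be small. The conclusion rests on reading the Measures list as the operative definition, since no other is shown. The primary outcome, the sample size, the disease-control outcomes and the economic analysis are unaffected.

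**What to change.** Add asthma (J45) to the list of diseases in the admissions item of secondary outcome 4, or state why it is excluded. Do this before any unblinded analysis, so that the choice cannot depend on the results. Leave the hospital cost definition as it is, without restriction by cause.

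The cost is one word in the outcome definition. If the data form repeats the three-disease list, it also needs one further field for cause of admission. Hospital use is already being collected, so no new visit or assessment is required.
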